## 4.2 Exclusion Criteria

Patients will be excluded from the study for any of the following reasons:

1. The patient requires concomitant therapy with any of the following: IL-2, interferon, or other non-study immunotherapy regimens; cytotoxic chemotherapy; immunosuppressive agents; other investigation therapies; any other systemic therapy for cancer including any other experimental treatment.

2. The patient requires chronic use of systemic corticosteroids. Systemic steroids for management of symptoms due to brain mets should be avoided if possible or subject should be stable on the lowest clinically effective dose. Topical or inhalational steroids are permitted.
3. Use of any investigational or non-registered product (drug or vaccine) other than the study treatment.
4. Active autoimmune disease: Patients with a history of inflammatory bowel disease, including ulcerative colitis and Crohn's Disease, are excluded from this study, as are patients with a history of symptomatic disease (eg, rheumatoid arthritis, systemic progressive sclerosis [scleroderma], systemic lupus erythematosus, autoimmune vasculitis [eg, Wegener's Granulomatosis]); motor neuropathy considered of autoimmune origin (e.g. Guillain-Barre Syndrome and Myasthenia Gravis).
5. Symptomatic CNS metastases (Remark: Asymptomatic stable, untreated or pretreated central nervous system (CNS) metastasis are allowed)
6. Family history of congenital or hereditary immunodeficiency.
7. The patient is known to be positive for Human Immunodeficiency Virus (HIV) or other chronic infections (HBV, HCV) or has another confirmed or suspected immunosuppressive or immunodeficient condition.
8. The patient has psychiatric or addictive disorders that may compromise his/her ability to give informed consent or to comply with the trial procedures.
9. Lack of availability for clinical follow-up assessments.
10. The patient has concurrent severe medical problems, unrelated to the malignancy, that would significantly limit full compliance with the study or expose the patient to unacceptable risk.
11. Other serious illnesses, e.g., serious infections requiring antibiotics or bleeding disorders.
12. Patients with serious intercurrent illness, requiring hospitalization.
13. For female patients: the patient is pregnant or lactating. Women of childbearing potential: Refusal or inability to use effective means of contraception
14. Any underlying medical or psychiatric condition, which in the opinion of the investigator will make the administration of ipilimumab hazardous or obscure the interpretation of AEs, such as a condition associated with frequent diarrhea.
15. Subjects with melanoma who have another active, concurrent, malignant disease are not eligible for this trial, with the exception of adequately treated basal or squamous cell skin cancer, superficial bladder cancer, or carcinoma in situ of the cervix.

#### 4.3 Justification of Gender

Within this clinical trial, no gender specific differences are expected concerning the efficacy and safety of the used study medication, so that it is not necessary to consider the gender during recruitment and evaluation or conception of this clinical trial. Therefore reasons according to §7 Abs. 2 Nr. 12 GCP V are not to apply.

## 5 STUDY THERAPY WITH IPILIMUMAB

### 5.1 Induction Treatment

Subjects enrolled after IC will receive ipilimumab according to the protocol of the completed Medarex study MDX010-20 (Hodi et al., NEJM, 2010) as a single agent at a dose of 3mg/kg for 4 times over 10 weeks (1 cycle): The day subjects receive the first dose of protocol ipilimumab therapy will define Day 1. Ipilimumab, 3 mg/kg, day 1 (W1), 22 (W4), 43 (W7), 64 (W10) must be administered intravenously over a 90-minute period every 3 weeks for a total of four doses, as tolerated. This dose demonstrated an overall survival benefit for the first time in treating metastatic melanoma in a controlled randomized clinical study (Hodi et al., NEJM, 2010).

- Electrocardiogram (ECG) examination should be performed during screening and week 12. Patients with an existing myocarditis are excluded from this study. For patients with suspicion of myocarditis e.g. dyspnoea, functional insufficiency etc. ECG examinations have to be performed before each treatment.
- Laboratory evaluations should be performed (refer to section 6.1.1.2) and the results examined before administration of each ipilimumab dose.
- As durable disease stabilization and/or objective tumor response can be seen after early progression before Week 12, it is recommended that, in the absence of dose-limiting toxicities (eg, serious irAEs), all four doses of ipilimumab be administered over the initial 12 weeks even in the setting of apparent clinical progression, providing the subject's performance status remains stable.
- All subjects who enter the induction period, including those who may have discontinued treatment for drug-related AEs should obtain a 12-week, 24-week 36-week and 48 week tumor assessment. Those patients who have evidence of clinical progression during the induction period, should obtain further tumor assessment according to Standard of Care.
- Based on clinical experience in the ongoing and completed melanoma studies, the following recommendations apply for subject management in light of the Week 12 or later tumor assessments:
  - The appearance of new lesions in subjects with other stable or shrinking baseline tumor burden may be experiencing clinical benefit and should continue in follow-up before alternative anti-cancer agents are considered. These subjects can be seen to have continued tumor shrinkage in follow-up scans.
  - Clinical progression warranting alternative anti-cancer treatment should be considered only in subjects whose overall tumor burden appears to be

substantially increased and/or in subjects whose performance status is decreased.

## 5.2 Re-Induction Treatment

Patients who have progressed following stable disease (SD) of  $\geq 3$  months duration from Week 12 assessment OR patients who have progressed following an initial response to the induction treatment (CR or PR diagnosed at week 12 assessment) may be offered additional cycles of therapy (4 infusions of ipilimumab 3mg/kg every 3 weeks) with the originally assigned treatment regimen ("Re-induction") until off-treatment criteria are met, provided they meet re-treatment criteria specified below.

- Re-treatment criteria:

Patients who received ipilimumab as induction in this study and have met each of the following criteria within **28 days** before re-treatment, are eligible for "re-induction":

- Had no unacceptable toxicity requiring ipilimumab discontinuation; OR
  - Patients who did not permanently discontinue treatment due to select irAEs as follows:
    - Reversible autoimmune hepatitis
    - Medically manageable endocrinopathy
    - Reversible dermatological toxicity
  - ECOG performance status of 0, 1 or 2
  - Electrocardiogram (ECG): during screening and week 12. Patients with an existing myocarditis are excluded from this study. For patients with suspicion of myocarditis e.g. dyspnoea, functional insufficiency etc. ECG examinations have to be performed before each treatment.
  - Patient must meet all other inclusion criteria as outlined before (see Inclusion criteria)
- AND
- Have experienced disease progression as documented by physical examination or diagnostic imaging (including brain imaging) after demonstrating expanded clinical benefit (see below).

All patients eligible for Re-induction treatment with ipilimumab their TSH level must be assessed at baseline and before each dose and the TSH level be available to the investigator prior to the administration of the dose. **The assessment of TSH is mandatory prior each treatment.** If a subject has thyroid dysfunction and concomitant symptoms (i.e. fatigue), the subject should be monitored more frequently and be treated as per standard medical practice.

The management algorithm for endocrine abnormalities is available on page 59 (appendix 10-15).

- Re-induction treatment:

During the Re-Induction treatment, subjects enrolled who are eligible for additional treatment cycles will repeat the treatment phase as outlined in INDUCTION TREATMENT. They will receive ipilimumab at the 3 mg/kg dose level every 3 weeks for the first 10 weeks (Weeks 1, 4, 7 and 10) of Re-induction.

Ipilimumab therapy should be offered to all subjects who have not experienced unacceptable toxicity (refractory Grade > 3 irAEs) and are considered by the investigator to be obtaining clinical benefit, either because of apparent tumor stability or continued shrinkage and/or late response. No patient will be re-treated if they experience a Grade 3 or higher nondermatologic autoimmune breakthrough event (ABE) considered related to study therapy or a Grade 3 or higher gastrointestinal or certain other immune-related adverse events (irAE) which require permanent discontinuation of ipilimumab (refer to section 5.5.3). If a patient has experienced a study medication-related dermatologic or non-dermatologic ABE < Grade 3, then the event must have improved to Grade 1 or less before re-treatment can be considered. No patient with disease progression following the first cycle of study medication will be permitted to be re-treated with study medication.

Patients can be eligible for more than one re-induction. The number of re-inductions is not limited. All re-inductions initiated while patient is on-study (**each patient study period**, first dosing + 12 months) will be performed in the frame of the study. Any re-induction starting after each patient study period (first dosing + 12 months) would be done outside of the study.

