**Appendix 7: Patient Information and Informed Consent**

## Appendix 8: irAE Treatment Algorithm

### Re-Induction:

Patients who progress following stable disease of  $\geq 3$  months starting from diagnosis at week 12 tumor assessment duration from beginning of induction treatment or or patients who have progressed following an initial response (partial or complete) assessed at week 12 may be offered additional cycles of therapy with the originally assigned treatment regimen until off-treatment criteria are met, provided they meet re-treatment eligibility requirements. Please note that progressive disease must be confirmed within not less than 4 weeks.

Re-induction is not allowed in patients who experience

- At least one Grade 3 or higher gastrointestinal immune-related adverse events (irAE) including, but not limited to,  $\geq$  Grade 3 colitis or diarrhea **OR**
- Uveitis of any grade **OR**
- At least one certain other immune-related adverse events (irAE) (refer to section 5.2 and 5.3) **OR**
- Disease progression following the first cycle of study medication

Exemption: Re-induction is allowed in patients who experience selected irAEs related to ipilimumab that have completely resolved with immunosuppressive therapy or are adequately controlled with hormone therapy, may be considered for further re-treatment with ipilimumab under this study, at the time of disease progression. The list of completely reversible or medically managed immune-related adverse events (irAEs) **eligible** for consideration is:

- Reversible autoimmune hepatitis
- Medically managed endocrinopathy
- Reversible dermatological toxicity

All other irAEs are not considered eligible for re-treatment!

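### Section 5.2 requires progression before re-induction, yet one sentence in it directs that ipilimumab be offered to all benefiting patients with stable or shrinking tumours

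*Protocol*

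**What the plan says.** Section 5.2 opens with two routes to re-induction, and both need progression. One is progression after stable disease of at least 3 months from the week-12 assessment. The other is "patients who have progressed following an initial response to the induction treatment (CR or PR diagnosed at week 12 assessment"). The list of re-treatment criteria repeats the requirement, joined to the other criteria by AND: "Have experienced disease progression as documented by physical examination or diagnostic imaging (including brain imaging) after demonstrating expanded clinical benefit (see below").

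Further down, under the re-induction treatment bullet, the section says: "Ipilimumab therapy should be offered to all subjects who have not experienced unacceptable toxicity (refractory Grade > 3 irAEs") and who, in the investigator's view, are benefiting, "either because of apparent tumor stability or continued shrinkage and/or late response". The same paragraph ends: "No patient with disease progression following the first cycle of study medication will be permitted to be re-treated with study medication". Section 5.1 describes induction as 3 mg/kg "for 4 times over 10 weeks (1 cycle").

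The Synopsis makes confirmed progressive disease a necessary condition for re-induction. Appendix 8 restates the rule with the 3 months counted from week 12, but the same sentence also carries the words "duration from beginning of induction treatment".

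**The concern.** A patient whose tumour is stable, still shrinking or responding late has not progressed. The opening of 5.2 and its criteria list exclude that patient from re-induction, while the later sentence directs that therapy be offered. The excluding rule is permissive (progressors may be offered treatment) and the conflicting sentence is directive, so a site cannot safely assume that the first overrides the second.

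Two things are at stake. The first is exposure: followed literally, the later sentence gives extra courses to patients whom the Synopsis and the rest of 5.2 exclude. Section 1.3.5.a reports possibly related deaths in 35 of 3800 patients across the programme (35/3800 = 0.9%). The second is interpretation. The Synopsis defines study treatment as induction plus re-induction of eligible patients, and the primary objective refers to treatment given as in MDX010-20. If sites apply eligibility differently, the single 1-year survival estimate covers a mixture of treatment policies.

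**Working it through.** The protocol gives no figure to reproduce here, so the check compares the texts, with one short calculation on the start point.

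**1. Disease status required.**
- Section 5.2, opening and criteria list: progression is required.
- Synopsis: progression is required and must be confirmed.
- Sections 1.2 and 1.5: re-induction in the case of relapse.
- Sections 1.3.6 and 1.4: progression after response or after stable disease of more than 3 months.
- Section 5.3: for patients with selected immune-related events, re-treatment is at the time of progression.
- Appendix 8: progression is required.
- Section 5.2, offer sentence: stability, shrinkage or late response, with no mention of progression.

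One sentence departs from a rule that is otherwise repeated consistently. Its reference to late response also does not match the response route in 5.2, which needs a response at week 12.

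**2. Can the offer sentence be read as harmless?** It follows text about patients already eligible for further cycles, so it could govern only those already in re-induction. The sentence does not say so. It addresses all subjects and sets no limit at the four infusions that make up a re-induction, and under 5.2 a further course would again need progression.

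**3. The first-cycle bar.** Under 5.1 one cycle is the whole four-dose induction. Taken literally, progression following the first cycle describes the very patients whom the opening of 5.2 admits. Other text points to a narrower meaning. Section 6.1.1.5 and the follow-up footnote to the Time and Events Schedule set apart patients who progress initially. Section 5.2 allows more than one re-induction, and section 3.6 provides for patients still in re-induction when their study period ends. In context the bar appears to mean progression as the first outcome of induction, but no passage states this.

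**4. Start point of the 3 months.** Scans are every 12 weeks. Take a patient with stable disease at week 12 and progression on the week-24 scan.
- Interval counted from week 12: 12 × 7 = 84 days.
- Three calendar months: 3 × 30.44 = 91.3 days. 84 < 91.3, so the patient does not qualify.
- Interval counted from the start of induction: about 24 × 7 = 168 days. 168 > 91.3, so the patient qualifies.

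This assumes calendar months and on-schedule scans. The protocol does not define a month in days; with 28-day months, 3 × 28 = 84 days and the week-12 count would just qualify. Section 5.2 also accepts progression found on physical examination, which need not fall on a scan date.

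**5. The benefit term.** The criteria list requires expanded clinical benefit and points below for its meaning. The only later text in 5.2 that describes benefit is the offer sentence, which does not use the term or present itself as a definition.

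**6. Effect on the analysis.** Section 9.5 measures survival from the first dose regardless of re-induction, and the primary denominator is everyone who received at least one dose. Neither depends on who is re-induced.

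**The case against.** The strongest reply is that this is a drafting slip in one sentence. The rule of progression after benefit appears in the Synopsis, five other sections and Appendix 8, and the Synopsis is explicitly restrictive. The offer sentence can be read as applying to patients already in re-induction, and it may be what the pointer to clinical benefit refers to. The second start point in Appendix 8 sits in broken syntax beside a doubled conjunction and looks like an editing remnant. Everywhere else the count starts at week 12 or, equivalently, at the first tumour assessment. Survival is counted regardless of re-induction.

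Most of this stands, and it limits the point. A reader might infer that eligibility is undefined; it is not, because the main rule is clear and repeated. A reader might also infer from the first-cycle bar that nobody could ever be re-induced; the provisions for repeated re-induction and for patients in re-induction at study end rule that out.

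The reply does not remove the conflict. The offer sentence is in the section that sites use to treat patients, it is directive, and nothing in it confines it to patients who have already progressed.

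**Conclusion.** Section 5.2 is internally inconsistent on who may be re-induced: its opening and criteria list require progression, and one sentence directs therapy to patients who have not progressed. The first-cycle wording, the stray start point in Appendix 8 and the unclear benefit term are lesser faults in the same rule.

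The number of patients affected cannot be derived. The protocol gives no disease-control rate at 3 mg/kg, and the effect depends on how many of up to 26 sites would follow the outlying sentence. The number of re-inductions per patient is unlimited, so exposure could differ by one or more courses.

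It would be too strong to conclude that the primary endpoint is compromised or that the regimen is no longer that of MDX010-20. The endpoint's definition, time origin and denominator are unchanged. Sections 1.3.6 and 1.4 describe the MDX010-20 regimen in terms close to the main rule of 5.2, so departure from it would arise only where a site applied the outlying sentence. The supportable conclusion is that exposure, and with it the regimen the 1-year survival estimate describes, could vary between sites. This is worth correcting.

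**What to change.** Reconcile the Synopsis, section 5.2 and Appendix 8 so that they carry one statement of the disease status required for re-induction and one start point for the 3 months. Within that:
- Remove the offer sentence, move it, or confine it expressly to the patients it is meant for.
- State which assessment or outcome the first-cycle bar refers to, given the definition of a cycle in 5.1.
- Delete whichever start point in Appendix 8 is not intended.
- Define expanded clinical benefit, or correct the pointer.

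Which rule stands is for the sponsor's clinical team. The cost is amendment wording only, with no change to sample size, endpoint or planned analysis.

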### **Re-induction:**

Patients who progress following stable disease of  $\geq 3$  months duration starting from diagnosis at week 12 tumor assessment or patients who have progressed following an initial response (partial or complete) assessed at week 12 may be offered additional cycles of therapy with the originally assigned treatment regimen until off-treatment criteria are met, provided they meet re-treatment eligibility requirements. Please note that re-induction is allowed only if progressive disease was confirmed within not less than 4 weeks. No patient will be re-treated if they experience a Grade 3 or higher gastrointestinal or certain other immune-related adverse events (irAE) (refer to section 5.2 and 5.3). No patient with disease progression following the first cycle of study medication will be permitted to be re-treated with study medication.

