### 5.3 Definition of Selected Reversible irAEs that May be Considered For Re-Treatment

Patients with selected irAEs related to ipilimumab that have completely resolved with immunosuppressive therapy or are adequately controlled with hormone therapy, may be considered for further re-treatment with ipilimumab under this study, at the time of disease progression. The list of completely reversible or medically managed immune-related adverse events (irAEs) eligible for consideration is:

- Reversible autoimmune hepatitis
- Medically managed endocrinopathy
- Reversible dermatological toxicity

All other irAEs are not considered eligible for re-treatment, including, but not limited to,

≥ Grade 3 colitis or diarrhea, or uveitis of any grade.

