#### 5.5.3.a *Permanent Discontinuation for Related Adverse Events*

**The following treatment related non-neurological adverse events require permanent discontinuation of ipilimumab:**

- Any  $\geq$  Grade 2 eye pain or reduction of visual acuity that does not respond to topical therapy and does not improve to  $\leq$  Grade 1 severity within 2 weeks of starting therapy, OR, requires systemic treatment.
- Any  $\geq$  Grade 3 bronchospasm or other hypersensitivity reaction.
- Any other  $\geq$  Grade 3 non-skin related adverse event with the exception of events listed under "No Discontinuation" (below).
  - Any  $\geq$  Grade 4 laboratory abnormalities, except AST, ALT, or Total Bilirubin
  - AST or ALT  $> 8 \times$  ULN
  - Total Bilirubin  $> 5 \times$  ULN
  - Any other  $\geq$  Grade 4 adverse event

- Any adverse event, laboratory abnormality or intercurrent illness which, in the judgment of the investigator, presents a substantial clinical risk to the patient with continued dosing.

Please refer to the IB for specific treatment algorithms.

**The following neurological adverse event requires permanent discontinuation of ipilimumab and defines unacceptable neurotoxicity:**

- Any motor neurologic toxicity  $\geq$  Grade 3 regardless of causality
- Any  $\geq$  Grade 3 treatment related sensory neurologic toxicity

Please refer to the IB for specific treatment algorithms.

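### Section 5.3 and Appendix 8 list hepatitis and endocrinopathy as eligible for re-induction without the grade 3 and permanent-discontinuation limits of 5.2

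*Protocol*

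**What the plan says.** Section 5.2 contains two restrictions. Its criteria list admits, besides patients without unacceptable toxicity, "Patients who did not permanently discontinue treatment due to select irAEs as follows": reversible autoimmune hepatitis, manageable endocrinopathy, reversible skin toxicity. Its text on the re-induction treatment adds a grade bar: "No patient will be re-treated if they experience a Grade 3 or higher nondermatologic autoimmune breakthrough event (ABE) considered related to study therapy". The same sentence goes on to gastrointestinal and certain other irAEs that require permanent discontinuation, and refers to 5.5.3. The way back is described only for milder events: "If a patient has experienced a study medication-related dermatologic or non-dermatologic ABE < Grade 3, then the event must have improved to Grade 1". A lower grade also satisfies this.

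Sections 1.2 and 1.5 limit re-induction to patients without any irAE of grade 3 or higher.

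Section 5.3 says that selected irAEs which "have completely resolved with immunosuppressive therapy or are adequately controlled with hormone therapy, may be considered for further re-treatment with ipilimumab under this study". It lists the same event types, with no grade and no condition on permanent discontinuation. Appendix 8 first bars patients with "certain other immune-related adverse events (irAE) (refer to section 5.2 and 5.3") and then continues: "Exemption: Re-induction is allowed in patients who experience selected irAEs related to ipilimumab that have completely resolved with immunosuppressive therapy", again without either limit.

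Section 5.5.3.a requires permanent discontinuation for related AST or ALT above 8 x ULN, for total bilirubin above 5 x ULN, and for any other related event of at least "Grade 3 non-skin related adverse event with the exception of events listed under" the exceptions. Section 5.5.3.b excepts hormone-controlled endocrinopathy; hepatitis is not on its list. The liver text in Appendix 10-15 (7.3.2) also requires a permanent stop above 8 x ULN for ipilimumab-related elevations. The hepatotoxicity algorithm that follows it tells sites to stop dosing until resolution and only to consider making the stop permanent.

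**The concern.** Whether a patient may be re-challenged after serious immune toxicity should not depend on which page the site opens. Appendix 8 is the one-page summary that a site is likely to use, and its exemption comes after bars that already refer to 5.2 and 5.3. Read as written, it lifts those bars for the listed events. The hepatotoxicity algorithm adds a second gap: if the stop is never made permanent, the patient also satisfies the 5.2 criterion that depends on it.

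What is at stake is patient safety and protocol compliance. The number of re-inductions is not limited, up to 26 sites take part, and section 1.4 names hepatic failure among the complications of irAEs. Two sites could decide differently on the same patient, each with a section to cite.

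A smaller inconsistency sits next to the bar. Section 5.2 says "Ipilimumab therapy should be offered to all subjects who have not experienced unacceptable toxicity (refractory Grade > 3 irAEs"), whereas 6.1.1 describes unacceptable toxicity as refractory irAEs of grade 3 or higher.

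**Working it through.** The plan gives no figure to reproduce here, so the check is mainly a comparison of text.

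| Place | Grade limit on hepatitis | Permanent discontinuation |
|---|---|---|
| 1.2 and 1.5 | no irAE of grade 3 or higher | not mentioned |
| 5.2, criteria list | none | must not have occurred |
| 5.2, treatment text | related grade 3 or higher is barred | named, with reference to 5.5.3 |
| 5.3 | none | not mentioned |
| Appendix 8, exemption | none | not mentioned |
| 5.5.3.a | grade 3 or higher, other non-skin events | required; also AST/ALT above 8 x ULN, bilirubin above 5 x ULN |
| Appendix 10-15, 7.3.2 Liver | not by grade | required above 8 x ULN |
| Hepatotoxicity algorithm | not by grade | only to be considered |

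Step 1. Hepatitis falls under the bar. Section 5.5.4 counts it among the presumptive autoimmune events now called irAEs, and it is not dermatologic.

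Step 2. Test case: related autoimmune hepatitis with ALT above 8 x ULN that resolves completely on corticosteroids, in a patient who responded at week 12 and later progresses.
- 5.5.3.a and 7.3.2: ipilimumab is permanently stopped.
- 5.2: not eligible, because treatment was permanently discontinued.
- 5.3: may be considered.
- Appendix 8, exemption: re-induction is allowed.
- Algorithm: dosing stops until resolution. If the site does not make the stop permanent, the 5.2 discontinuation criterion no longer excludes the patient.

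Step 3. The test case is not far-fetched. In 7.3.2 high-dose corticosteroids start above 8 x ULN, the level at which ipilimumab is permanently stopped. Hepatitis that resolved on immunosuppression can therefore be the very event that 5.5.3.a excludes.

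Step 4. Size. Table 3 in section 1.3.5.b (CA184-022, 3 mg/kg, N = 71) gives 0% grade 3-4 hepatic irAEs, that is 0/71. The Clopper-Pearson 95% upper limit is 1 - 0.025^(1/71) = 0.0506, or 5.1%. For 200 patients this is 0 expected, with an upper limit of 200 x 0.0506 = 10.1. Only re-induced patients matter. The protocol gives no re-induction fraction f, so f is an assumption: the upper limit becomes 0.5 (f = 5%), 1.0 (10%), 2.0 (20%) or 3.0 (30%). Higher-dose data are left out because 1.3.5.b reports that irAE frequency depends on dose. Grade 3-4 hepatic events are only a proxy for hepatitis meeting the permanent-stop criteria.

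Step 5. Endpoint. Section 9.5 measures survival from the first dose regardless of re-induction, so the analysis rule is unaffected.

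**The case against.** The best defence is that the rules are cumulative. Section 5.3 defines event types and says only that patients may be considered; 5.2 supplies the limits. Appendix 8 opens by requiring that re-treatment eligibility be met, and both it and the synopsis cite 5.2 and 5.3 together. Sections 1.2 and 1.5 show that grade 3 was the intended ceiling. There are also practical safeguards: 7.3.2 asks for contact with the medical monitor from grade 2 liver values, and 5.5.2 asks the investigator to contact the PI about any event that leads to a skipped dose or discontinuation.

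Much of this stands for 5.3. It does not settle Appendix 8, where the exemption is placed after bars that already cite 5.2 and 5.3 and so reads as overriding them. Section 5.3 also attaches a grade to colitis and diarrhea, and names any grade for uveitis, so its silence on hepatitis can be read as no limit. The algorithm does say that permanent discontinuation is to follow the protocol, but it points to a section 6.2.5 that this protocol does not have.

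Two further objections limit the point:
- The stricter reading of the grade conflict, that resolved grade 3 hepatitis between 5 and 8 x ULN is barred in one place and allowed in another, needs that window to be grade 3. The CTCAE cut-offs are not reproduced in the protocol, so this is an assumption.
- For hormone-controlled grade 3 endocrinopathy the conflict disappears if the reference to 5.5.3 covers the whole bar in 5.2, because 5.5.3.b then applies.

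The mismatch between refractory grade above 3 and grade 3 or higher could be a typing slip or a sign lost in reading the PDF. The stricter bar in the next sentence of 5.2 governs in any case.

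**Conclusion.** The inconsistency is real and should be corrected. Section 5.2, with 5.5.3.a, excludes patients whom 5.3 and the Appendix 8 exemption admit on their wording, and the algorithm softens a stop that 5.5.3.a and 7.3.2 make mandatory. For hepatitis that met a permanent-stop criterion, this holds whichever way the 5.2 sentence is parsed.

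The number affected is small. The hepatic estimate at the protocol dose is zero (0/71, upper limit 5.1%), or at most about 1 to 2 re-induced patients at the upper limit if 10-20% are re-induced, which is an assumption.

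A reader might infer three stronger conclusions that the documents do not support:
- That about one patient in the trial will be affected. That figure comes from endocrine events (2/71 = 2.8%; 200 x 2.8% = 5.6; times 10-20% gives 0.6 to 1.1). It rests on the assumed fraction and on a reading of 5.2 that denies the 5.5.3.b exception.
- That the one-year survival result is compromised. It is not materially changed, since survival is measured regardless of re-induction and few patients are involved.
- That the protocol ought to cap hepatitis at grade 2 or endocrinopathy at grade 3 as new policy. Such ceilings are a clinical decision for the sponsor; the point here is only that the protocol must state one rule.

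**What to change.** 1. In 5.3 and in the Appendix 8 exemption, state that the listed irAEs qualify only if no permanent-discontinuation criterion of 5.5.3.a was met, subject to the exceptions in 5.5.3.b (including hormone-controlled endocrinopathy), and only if the grade 3 bar in 5.2 is respected.
2. In the hepatotoxicity algorithm, require permanent discontinuation above 8 x ULN, in line with 5.5.3.a and 7.3.2, and correct the section reference.
3. In 5.2, change the refractory-irAE cut-off to grade 3 or higher to match 6.1.1, after checking the sign in the source document.
4. If the sponsor wishes to admit resolved grade 3 hepatitis at or below 8 x ULN, write it as an explicit exception in 5.2. That choice is the sponsor's.

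The cost is one wording amendment and a notice to sites. Data collection, sample size and analysis do not change.
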